## Abstract

**Background:**

Substance use and abuse is a growing problem among adolescents with mild to borderline intellectual disabilities (ID). Substance use patterns in general population are similar to patterns among non-disabled peers, but substance use has more negative consequences for adolescents with mild to borderline ID, and they are at an increased risk for developing a substance use disorder. Nevertheless, effective and evidence based prevention programs for this groups are lacking. The study described in this protocol tested the effectiveness of a selective intervention aimed at reducing substance use in adolescents with mild to borderline ID and behavioral problems. In the intervention, participants acquire competences to deal with their high-risk personality traits.

**Methods:**

A randomized controlled trial will be conducted among 14–21-year old adolescents with mild to borderline ID and behavioral problems admitted to treatment facilities in the Netherlands. Inclusion criteria are previous substance use and personality risk for substance use. Participants will be individually randomized to the intervention (n = 70) or control (n = 70) groups. The intervention group will be exposed to six individual sessions and five group sessions carried out by two qualified trainers over six-week period. Primary outcomes will be the percentage reduction in substance use (for alcohol: percentage decrease of binge drinking, weekly use and problematic use, for cannabis: the percentage decrease of lifetime cannabis use and weekly use and for hard drug: the percentage decrease of lifetime use). Secondary outcomes will be motives for substance use, intention to use, and internalizing and externalizing behavioral problems. All outcome measures will be assessed after two, six, and twelve months after the intervention.

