## Background

Substance use and abuse is a problem among adolescents and young adults with mild to borderline intellectual disabilities (ID), and both scientists as practitioners report increasingly number of concerns about this subject [1–4]. The results of an explorative study in the Netherlands showed that 75 %-85 % of adolescents with mild to borderline ID and severe behavioral problems who are admitted to treatment facilities show lifetime alcohol use or use of alcohol on a regular basis. Moreover, 25 %-50 % of the described target group uses drugs (in particular cannabis) occasionally or regularly. For most cannabis users, cannabis is a part of their daily habit [5, 6]. Although patterns of cannabis use are quite similar to substance use patterns among non-disabled peers, this is of great concern because substance use and misuse have more negative consequences [1, 5, 7] for adolescents with mild to borderline ID. Substance use by these adolescents causes various problems, including social, mental and behavioral problems, criminal activities, and financial problems [4]. Adolescents are also at a higher risk for developing a substance use disorder [6, 8, 9] compared to their nondisabled peers. To limit these negative consequences, the development of prevention programs that are adjusted to the needs of adolescents with mild to borderline ID is necessary. However, currently well-fitting and evidence-based prevention programs for adolescents with mild to borderline ID and substance use are lacking [10–12].

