After selecting the treatment centers, adolescents will complete a screening questionnaire to identify adolescents who meet the inclusionary criteria. Adolescents will be eligible to enter the trial if they meet the following inclusion criteria: (1) life time prevalence of alcohol, cannabis, or hard drug use, (2) belonging to one of the four personality high-risk groups (SS, IMP, AS or NT), and (3) providing signed informed consent along with the signed informed consent from parents or legal representative. Adolescents scoring more than one standard deviation above the sample mean on one of the four high-risk personality scales of the Substance Use Risk Profile Scale (SURPS) [40] will be classified as belonging to that risk profile. Adolescents who will score above the average on more than one personality profile will be assigned to the profile for which they showed the largest statistical deviation with respect to the z-score (cf. [17]). Adolescents with addiction problems will be excluded from participation in the intervention and the trial because this intervention is not considered sufficient for them. For these adolescents, treatment will be organized in collaboration with a regional institute for addiction care. Parents or legal representatives will be informed about the study through a letter sent home, asking them to contact the researchers by phone or email if they do not wish their child to participate in the screening (passive informed consent). Adolescents will be informed on the day of the screening, at which time they have the option not to participate in the trial. Parents (when participants are under the age of 18 years) and adolescents will need to provide active informed consent to participate in the RCT. After the screening questionnaire and informed consent, the adolescents will be individually randomized to either control condition or experimental condition.

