### Outcomes

‘Take it Personal!’ aims to decrease substance use among adolescents with mild and borderline ID. We operationalized goals for limiting alcohol, cannabis, and hard drug use. The primary outcome of alcohol use will be the percentage of decrease in binge drinking, weekly use, and problematic use. The primary outcomes of cannabis use will be the percentage of decrease in lifetime cannabis use and weekly use. The primary outcome of hard drug use will be the percentage of decrease in lifetime use. These outcome measures will be assessed at baseline and two, six, and twelfth months after the intervention using the Substance Use and Misuse among Intellectually Disabled Persons Questionnaire (SumID-Q; [43]). This questionnaire is specifically developed to measure substance use among people with intellectual disabilities. Secondary outcomes are the intention to use less alcohol and/or drugs in the future [44, 31], motives for alcohol and/or drug use (Drinking Motives Questionnaire-Revised-Short Form (DMQ-R-SF) [45], and internalizing and externalizing behavioural problems measured by YSR [46]. Adolescents with mild to borderline ID are able to complete self-report instruments with some support [47]. Therefore, all measures will be supported using structured interviews.

This study examined the effectiveness of ‘Take it Personal!’ in daily practice (effectiveness trial). In this case, it is important to monitor the program fidelity [48, 49]. For this reason, we will monitor five domains: 1) adherence, 2) exposure (dosage), 3) quality of the delivery, 4) responsiveness of the participant, and 5) program differentiation (cf. [49]).

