### Statistical analysis

Descriptive analyses will be conducted to examine whether the randomization results in a similar distribution of demographic factors and outcome measures in both conditions. Variables that show different distributions between the two groups will be entered as confounders in all models testing the effectiveness of the intervention. The effect of the intervention program on the primary and secondary outcome variables will be tested in accordance with the intention-to-treat principle and in a completers-only framework by using Mplus [50]. Intention-to-treat means that all participants will be analyzed in the condition to which they will be assigned by randomization. Missing data will be handled by multiple imputation (MI). A total of 20 datasets will be completed by multiple imputation. Mplus will read the 20 datasets via the TYPE = IMPUTATION option and will carry out the desired analyses for each dataset. Mediating the parameter estimates will then aggregate the results for the 20 analyses. With respect to the completers-only analyses, only the participants with scores for all time points will be included. In both the intention-to-treat and the completers-only analyses, the effect of the intervention condition will be compared to the control condition. Because the data have a multilevel structure (i.e., individuals are ‘clustered’ within treatment centres), the individual respondents within treatment centres may be interdependent. To correct for the potential non-independence (complexity) of the data, the TYPE = COMPLEX procedure in Mplus will be used. This procedure corrects the standard errors of the parameter estimates for dependency, leading to unbiased estimates. The results of the study will be reported in accordance with the CONSORT statement [51, 52].

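### Every primary outcome is a percentage decrease at an unstated level: undefined at zero baseline if per participant, imprecise if per arm, and unable to fall for the two lifetime-use outcomes

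*Protocol article*

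**What the plan says.** The Abstract (Methods) and the Outcomes section state the primary outcomes in the same form. The Abstract has: "Primary outcomes will be the percentage reduction in substance use". The Outcomes section has, for alcohol: "The primary outcome of alcohol use will be the percentage of decrease in binge drinking, weekly use, and problematic use". For cannabis: "The primary outcomes of cannabis use will be the percentage of decrease in lifetime cannabis use and weekly use". For hard drugs: "The primary outcome of hard drug use will be the percentage of decrease in lifetime use". That makes six measures, each a percentage decrease. Neither section says whether the percentage is worked out for each participant or for each arm, and neither gives a rule for a baseline of zero.

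The first inclusion criterion under Recruitment is "life time prevalence of alcohol, cannabis, or hard drug use". Having ever used any one substance is enough, and current use of each is not required. Adolescents with addiction problems are excluded.

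Under Statistical analysis: "Intention-to-treat means that all participants will be analyzed in the condition to which they will be assigned by randomization". Missing data are handled with 20 imputed datasets, and a completers-only analysis is added. Baseline outcome measures enter the models as confounders only if their distributions are seen to differ between the arms.

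**The concern.** A percentage decrease needs a non-zero starting value. A participant who qualified through alcohol alone starts at zero on weekly cannabis use; one who drinks occasionally may start at zero on binge drinking and problematic use. For that person the individual percentage is 0/0, and starting to use has no finite value. Imputation does not help, because the value is undefined rather than missing.

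If the percentage is instead the fall in each arm's prevalence, nobody is lost and new users count. But each arm's result is then divided by its own baseline count. Randomisation makes that division unnecessary, and with about 63 evaluable participants per arm it adds noise, most where prevalence is low.

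The lifetime-use outcomes have a further problem on either reading: someone who has ever used remains an ever-user.

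At stake are whether the primary outcome can be computed for everyone randomised, how much power is given up, and whether two of the six outcomes can show the hypothesised reduction at all.

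**Working it through.** **1. The plan's own figure.** From Power analyses: f = 0.25, two-sided alpha 0.05, power 0.80, 10% loss to follow-up. For two groups d = 2f = 0.50. Per arm, n = 2 × (1.96 + 0.842)² / 0.50² = 62.8, so 63; then 126 / 0.9 = 140. The stated 140 reproduces and is not challenged. It supplies the 63 per arm used below.

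**2. Per-participant reading.** Individual percentage decrease = (baseline − follow-up) / baseline. At baseline 0 and follow-up 0 this is 0/0; at baseline 0 and follow-up above 0 it has no finite value. Recruitment lets such participants in, and Statistical analysis promises to analyse all of them. Both cannot be met for that outcome without a further rule.

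**3. Per-arm reading, by example.** Arm percentage decrease = 1 − (follow-up users / baseline users). Suppose 63 per arm, with 19 baseline users in control and 13 in intervention, and 13 users in each arm at follow-up.

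- Control: 1 − 13/19 = 32%. Intervention: 1 − 13/13 = 0%.
- The arms are identical at follow-up, yet the percentage decreases differ by 32 points.
- Baseline difference: 6/63 = 9.5 points. Pooled prevalence is 32/126 = 0.254 and its standard error √(0.254 × 0.746 × 2/63) = 0.078, so z = 1.2. This is ordinary chance imbalance, and a check for differing distributions could easily pass it.

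**4. Power.** Assumed inputs, none given in the article: baseline and control follow-up prevalence 25% with intervention 10%, or 50% with intervention 26%; yes/no pairs cut from latent normal variables with baseline–follow-up correlation 0.3, 0.6 or 0.8; 63 per arm; no clustering by centre. Three analyses, 10,000 runs per setting:

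- A: follow-up status among baseline users only (two-proportion z test).
- B: per-arm percentage decrease, tested as the difference in log(follow-up users / baseline users). The variance per arm is 1/y + 1/b − 2c/(yb), with y follow-up users, b baseline users and c users at both times.
- C: follow-up status in all, regressed on arm and baseline status, with robust standard error.

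| Prevalence | Correlation | A % | B % | C % | C − B | C − A |
|---|---|---|---|---|---|---|
| 25 v 10 | 0.3 | 25.3 | 44.7 | 61.7 | 17.0 | 36.4 |
| 25 v 10 | 0.6 | 33.8 | 55.0 | 67.4 | 12.4 | 33.6 |
| 25 v 10 | 0.8 | 47.9 | 68.5 | 75.6 | 7.1 | 27.7 |
| 50 v 26 | 0.3 | 54.6 | 67.1 | 81.4 | 14.3 | 26.8 |
| 50 v 26 | 0.6 | 63.6 | 79.4 | 86.2 | 6.8 | 22.6 |
| 50 v 26 | 0.8 | 75.0 | 89.0 | 91.6 | 2.6 | 16.6 |

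With no true effect, rejection was 4.4% to 5.5% for all three (5,000 runs each). A separate run over the same correlation range gave gaps of about 4 to 22 points (C − B) and 17 to 39 points (C − A). The ordering C above B above A held in every setting tabulated. The gap narrows as correlation rises.

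**5. Lifetime use.** Ever-use at baseline implies ever-use at follow-up. In a fixed group, lifetime prevalence can therefore only stay level or rise; an apparent fall would reflect inconsistent reporting or selective dropout. This affects two of the six outcomes: lifetime cannabis use and lifetime hard drug use.

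**The case against.** A reader might infer that participants who do not use a substance at baseline will be dropped, that intention-to-treat is therefore breached, and that prevention of new use is left out of the endpoint. The article does not support this. Nowhere does it plan to exclude non-users; it says the opposite, and its completers-only set is defined by having scores at all time points, not by baseline use. Binge drinking, weekly use, problematic use and lifetime use read most naturally as yes/no states, which favours the per-arm reading. On that reading there is no 0/0, everyone randomised counts, and a participant who starts using raises the arm's prevalence. All of this stands, so the per-participant problem is conditional and the 17 to 39 points describe an analysis that nobody has announced.

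It is also fair that the confounder rule deals with some baseline imbalance, and that a condensed article may leave the model for each outcome to an analysis plan. But that rule acts only when a difference is noticed. And the form of the primary outcome is not left open: it is stated twice as a percentage decrease.

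Finally, the power figures rest on assumed prevalences and correlations. At high correlation the cost of the per-arm form is small.

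**Conclusion.** The point holds in this form: the primary outcomes are fixed as a percentage decrease whose level is unstated, and neither reading serves the trial well. Per participant, the outcome cannot be computed for baseline non-users, so the stated analysis of all randomised participants could not be carried out for it. Per arm, it is defined for everyone but less precise than a baseline-adjusted comparison of follow-up status, by about 3 to 22 points of power under the assumptions shown. On either reading, two of the six outcomes cannot show a true reduction.

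The size depends on the assumed prevalences, effects and correlations (0.3 to 0.8) and on ignoring clustering. The preference for the adjusted analysis held in every setting tried. The sample size arithmetic is sound. The change is worth making, but the article as written does not amount to a breach of intention-to-treat.

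**What to change.** - Define binge drinking, weekly alcohol use, problematic alcohol use and weekly cannabis use each as yes/no status at a named follow-up, in all randomised participants.
- Compare the arms with a model that always includes baseline status of the same behaviour, whether or not the arms are seen to differ on it. Report an adjusted risk difference or risk ratio with 95% CI.
- Keep percentage decrease as a description only, and say that it is calculated per arm.
- For cannabis and hard drugs, replace lifetime use with use in a recent period covered by the follow-up questionnaire. If the questionnaire does not record such a period, relabel the outcome as new onset among those who had never used at baseline. A yes/no version of lifetime use would not be enough, because it still cannot fall.

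The cost is wording of outcomes and model. Participants, visits and sample size stay as they are. The first four outcomes use data already planned at baseline and follow-up. For recent hard drug use, someone must first check that the questionnaire covers it, since the article does not say.

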**Discussion:**

This study protocol describes the design of an effectiveness study of a selective prevention program for substance use in adolescents with mild to borderline ID and behavioral problems. We expect a significant reduction in alcohol, cannabis and hard drug use among adolescents in the intervention group compared with the control group.

**Trial registration:**

This trial is registered in the Dutch Trial Register (Cochrane Collaboration) as NTR5037 registered at 15 April 2015.

## Background

Substance use and abuse is a problem among adolescents and young adults with mild to borderline intellectual disabilities (ID), and both scientists as practitioners report increasingly number of concerns about this subject [1–4]. The results of an explorative study in the Netherlands showed that 75 %-85 % of adolescents with mild to borderline ID and severe behavioral problems who are admitted to treatment facilities show lifetime alcohol use or use of alcohol on a regular basis. Moreover, 25 %-50 % of the described target group uses drugs (in particular cannabis) occasionally or regularly. For most cannabis users, cannabis is a part of their daily habit [5, 6]. Although patterns of cannabis use are quite similar to substance use patterns among non-disabled peers, this is of great concern because substance use and misuse have more negative consequences [1, 5, 7] for adolescents with mild to borderline ID. Substance use by these adolescents causes various problems, including social, mental and behavioral problems, criminal activities, and financial problems [4]. Adolescents are also at a higher risk for developing a substance use disorder [6, 8, 9] compared to their nondisabled peers. To limit these negative consequences, the development of prevention programs that are adjusted to the needs of adolescents with mild to borderline ID is necessary. However, currently well-fitting and evidence-based prevention programs for adolescents with mild to borderline ID and substance use are lacking [10–12].

### Take it personal!

‘Take it personal!’ is a selective prevention program aimed at reducing substance use in adolescents with mild to borderline ID [13]. The program is specifically developed for adolescents with mild to borderline ID who receive treatment for additional behavioral problems. It is a selective intervention targeting adolescent who initiated substance use and who have a personality risk for substances. ‘Take it personal!’ offers adolescents competences to deal with their personality traits and associated motives for excessive substance use. The program is based on an existing program for non-disabled peers that have been proven to be effective [14–17] and is based on the theory that personality is an important construct for understanding adolescents’ substance use and misuse [14]. Four personality profiles are identified to be associated with substance use namely, Sensation Seeking (SS), Impulsivity (IMP), Anxiety Sensitivity (AS), and Negative Thinking (NT) [14]. Each personality profile is associated with unique patterns of substance use, maladaptive motives for substance use, and comorbid psychopathology [18–20]. Sensation seekers are more likely to be heavy drinkers and have greater risk for adverse drinking consequences [21, 22]. Impulsivity is associated with increased risk for early onset of alcohol and drug problems [23]. The lack of ability to delay behavioural response in impulsive individuals [24] is a risk factor for abuse of drugs due to a self-regulation deficit [25]. Highly anxious sensitive persons showed increased levels of drinking [26, 27] are more responsive to the anxiety-reducing effect of alcohol, are more likely to use alcohol to cope with negative feelings [28], and have a higher incidence of problem drinking symptoms [29]. They often cope with their negative feelings by using a combination of withdrawal (from social situations), dependence (on others to make them feel better), or use of alcohol and/or drugs. Persons with high levels of hopelessness usually use alcohol and/or drugs to cope with negative feelings [14, 28, 30, 31]. The intervention offers adolescents competences to deal with their personality traits and associated motives for substance use. Previous studies on interventions based on these personality profiles have demonstrated that this intervention is effective for adolescents with normal intelligence [14–17]. These personality profiles have not been applied in interventions targeting adolescents with mild and borderline ID, while they might be particularly relevant for this high-risk target group, as personality related substance use and psychopathology is highly prevalent in this population.

The intervention is based on the theoretical principles of motivational interviewing (MI) and cognitive behavioral therapy (CBT), the techniques that have been proven to be effective by decreasing alcohol and drug use among non-disabled adolescents [32–35]. Scientific evidence also shows that these techniques are effective for people with mild to borderline ID [36–38].

The intervention for adolescents with mild to borderline ID was developed according to the guidelines for effective interventions for people with mild ID [39]. We used simple information; offered concrete exercises and games; used more visual materials (like pictures), short sessions, and more sessions for repetition. Furthermore, we used techniques of psychomotor therapy. Psychomotor therapy is a common method used by adolescents with ID, and practitioners have good experiences in daily practice. This intervention will fill a gap in existing prevention programs for adolescents with mild to borderline ID.

### Aims and hypotheses

The main aim of this study is to test the effectiveness of the intervention ‘Take it personal!’ in decreasing substance use among adolescents (age 14 – 21 years old) with mild to borderline ID and behavioral problems who are admitted to treatment facilities in the Netherlands. The effectiveness of the intervention is being assessed by conducting a randomized controlled trail (RCT) with two conditions (treatment and control group). Follow-up assessments will be carried out at two, six, and twelve months after the start of the intervention.

The main hypothesis is that the intervention will reduce alcohol, cannabis, and hard drug use among individuals in the intervention group compared to those in the no-intervention control group. We also expect a decrease in the intention to use alcohol, cannabis and/or hard drugs in the future, a change in motives for alcohol and/or drug use after two, six, and twelfth moths in the intervention group compared with the control group. In addition, the effect of the program on internalizing and externalizing behavioral problems will be tested after two, six and twelve months after start of the intervention. We hypothesized that the intervention would decrease internalizing and externalizing behavioral problems in the intervention group compared with the control group.

